## Abstract

**Background:**

Sexual and gender minority (SGM) young people are disproportionately affected by HIV in the United States, and substance use is a major driver of new infections. People who use web-based venues to meet sex partners are more likely to report substance use, sexual risk behaviors, and sexually transmitted infections. To our knowledge, no machine learning (ML) interventions have been developed that use web-based and digital technologies to inform and personalize HIV and substance use prevention efforts for SGM young people.

**Objective:**

This study aims to test the acceptability, appropriateness, and feasibility of the uTECH intervention, a SMS text messaging intervention using an ML algorithm to promote HIV prevention and substance use harm reduction among SGM people aged 18 to 29 years who have sex with men. This intervention will be compared to the Young Men’s Health Project (YMHP) alone, an existing Centers for Disease Control and Prevention best evidence intervention for young SGM people, which consists of 4 motivational interviewing–based counseling sessions. The YMHP condition will receive YMHP sessions and will be compared to the uTECH+YMHP condition, which includes YMHP sessions as well as uTECH SMS text messages.

**Methods:**

In a study funded by the National Institutes of Health, we will recruit and enroll SGM participants (aged 18-29 years) in the United States (N=330) to participate in a 12-month, 2-arm randomized comparison trial. All participants will receive 4 counseling sessions conducted over Zoom (Zoom Video Communications, Inc) with a master’s-level social worker. Participants in the uTECH+YMHP condition will receive curated SMS text messages informed by an ML algorithm that seek to promote HIV and substance use risk reduction strategies as well as undergoing YMHP counseling. We hypothesize that the uTECH+YMHP intervention will be considered acceptable, appropriate, and feasible to most participants. We also hypothesize that participants in the combined condition will experience enhanced and more durable reductions in substance use and sexual risk behaviors compared to participants receiving YMHP alone. Appropriate statistical methods, models, and procedures will be selected to evaluate primary hypotheses and behavioral health outcomes in both intervention conditions using an α<.05 significance level, including comparison tests, tests of fixed effects, and growth curve modeling.

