### This Study

We hypothesize that the uTECH+YMHP intervention will be considered acceptable, appropriate, and feasible by most participants. Furthermore, we hypothesize that participants receiving the combined uTECH+YMHP intervention will show greater and more sustained reductions in substance use and sexual risk behaviors compared to those receiving the YMHP intervention alone. Specifically, we anticipate that the integration of ML-informed SMS text messages will enhance the efficacy of YMHP counseling methods by providing personalized, timely, and contextually relevant support, ultimately leading to improved health outcomes in this sample of SGM young adults.

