### The uTECH Intervention

Participants randomized to receive the uTECH intervention (uTECH+YMHP) will receive SMS text messages that use the Information-Motivation-Behavior Skills (IMB) model [51] to improve substance use harm reduction and promote safer sex practices. The IMB model was developed to use information, motivation, and behavioral skills to promote HIV-related behavior change, positing that when groups at risk for HIV are well informed, motivated to act on their knowledge, and have the necessary behavioral skills to seek out and initiate change, they will successfully overcome obstacles to make behavior change. The IMB model is effective in enhancing protective health behaviors such as adherence to interventions or reduction of risk behaviors with people living with HIV or AIDS [52-54] and people who use substances [55-57].

Staff will follow the IMB framework to generate content for the SMS text messages, a process that will be informed by an extensive review of public health messaging, scientific literature, and validated survey instruments tailored for specific subgroups that will be recruited for this study. The groups include people who inject drugs, people who do not inject drugs, people who are on PrEP, people who are not on PrEP, transgender and nonbinary people who are on PrEP, and transgender and nonbinary people who are not on PrEP. Each participant will be assigned to 1 of the above subgroups based on their answers in their baseline interview. The SMS text messages will be sent to participants using Twilio (version 8.0.0; Twilio Inc) [58], a web-based communications service that can be programmed to send and receive SMS text messages. Approximately 2 SMS text messages will be scheduled per week, so that each participant will receive 100 text messages over the course of 12 months.

To obtain feedback, participants will be asked to respond to each SMS text message. Participants will be compensated US $1 per SMS text message to which they reply. Each SMS text message also includes an opt-out option to comply with cell carrier antispam policies. The feedback from participants will also be used to enhance the ML algorithm in preparation for fully automated SMS text message generation and assignment (Table 1).

**Table 1 table1:** Text message content examples from the uTECH intervention using the Information-Motivation-Behavior Skills (IMB) model.

	PrEP^a^ initiation	PrEP adherence	Sexual risk reduction	Substance use harm reduction

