#### YMHP Sessions (All Participants)

##### Overview

YMHP intervention sessions will be held over Zoom, a videoconferencing platform. Session 1 will take place during week 1 (following onboarding), session 2 during week 2, session 3 during month 1, and session 4 during month 2 (Figure 1). All sessions will be audio recorded for intervention fidelity and ongoing intervention training and clinical support. No video or participant names will be captured for the recording. Participants will be asked to change their Zoom name to their participant ID before recording.

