### Discharge From the Study

Participants will be discharged from the study after they complete their 12-month assessment and offboarding. At their final interview, Android-using participants will receive instructions on how to uninstall the eWellness app from their phone. The study team will also discontinue sending automated SMS text messages to uTECH+YMHP participants.

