### Secondary Outcomes

The overall framework of this study recognizes that substance use and sexual risk behaviors are primary drivers of HIV and other STIs, which will be assessed through self-reported data on sexual risk, substance use, and self-reported HIV and STI diagnosis, verified through independent medical chart review when submitted by participants. Intimate partner violence, stigma, sociodemographic factors, and use of web-based venues for sex or drug seeking are potential risk factors for HIV and other STIs [63-66]. PrEP use, vaccination, and condom use are potential health protective behaviors. For all participants, we posit that YMHP can also help participants make positive changes toward their self-defined substance use and sexual health goals. For participants in the uTECH+YMHP condition, uTECH can improve participants’ skills and motivation to make behavioral changes to improve their health, which may lessen their risk of acquiring HIV and other STIs. In addition, we posit that in this combined condition, positive behavior changes may be more sustainable and durable compared to receiving YMHP without uTECH.

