### Expected Timeline

Development of the initial version of eWellness was completed in October 2020, and enrollment for the trial started soon after. The eWellness app continued to undergo refinement and development until phase 2 began in November 2021. Enrollment will continue until the target sample size is reached, with 12 months of study engagement per participant. We expect to complete data collection 12 months after the last participant has been enrolled in the study, that is, by June 2024, and plan the dissemination of results subsequently.

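### The design can show whether reductions are better maintained while uTECH texting continues, but not whether any added uTECH effect persists after messaging stops

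*Protocol article*

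**What the plan says.** The behavioural hypothesis appears in three places in the protocol article. The abstract (Methods) says the combined arm "will experience enhanced and more durable reductions in substance use and sexual risk behaviors". This Study says participants in that arm "will show greater and more sustained reductions in substance use and sexual risk behaviors". Secondary Outcomes posits that in the combined condition "positive behavior changes may be more sustainable and durable compared to receiving YMHP without uTECH".

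The YMHP Sessions overview schedules "session 3 during month 1, and session 4 during month 2", so counselling ends in month 2 in both arms. For texting, The uTECH Intervention says that at about 2 messages a week "each participant will receive 100 text messages over the course of 12 months", with US $1 for each reply. Under Discharge From the Study, "Participants will be discharged from the study after they complete their 12-month assessment and offboarding", and at that point "The study team will also discontinue sending automated SMS text messages to uTECH+YMHP participants". Expected Timeline adds: "We expect to complete data collection 12 months after the last participant has been enrolled in the study". Assessments are at baseline and 3, 6, 9 and 12 months.

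Planned Analytic Approach models months 3 to 12 with latent growth factors. It reads an intercept difference as a post-intervention effect and a slope difference as different trajectories. Missing Data likewise describes treatment-effect analyses as concerning differences once the intervention is over.

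**The concern.** In ordinary use, a durable effect is one that outlasts the intervention. In the YMHP-only arm every follow-up comes after counselling has ended. In the combined arm the added component is still being delivered, with reply payments, for essentially the whole of follow-up. A better 12-month result or a more favourable slope with uTECH fits lasting behaviour change. It fits equally well an effect that holds only while prompts and payments continue.

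The analysis text makes the first reading more likely, because it labels follow-up as post-intervention without distinguishing the arms. The risk is a report that uTECH's benefit persists without further messaging. That would matter to anyone planning a later trial or roll-out, because it bears on whether messaging has to be kept up.

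**Working it through.** The protocol gives no figure to reproduce. The question is one of timeline and of what the data can identify.

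**Inputs**
- Last counselling session: month 2, both arms (YMHP Sessions overview; YMHP Scheduling).
- Texts: about 2 a week, 100 over 12 months (The uTECH Intervention; Automated SMS Text Messages).
- Texts discontinued: at discharge, after the 12-month assessment (Discharge From the Study).
- Follow-up assessments: months 3, 6, 9 and 12, none later (Assessment Measures; Expected Timeline).

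**Step 1: length of texting.** 100 messages / 2 per week = 50 weeks. Twelve months is 52 weeks, and 52 − 50 = 2. If texting starts at onboarding and runs at exactly 2 a week, at most about 2 weeks before month 12 are free of texts. A later start or a slightly slower rate closes that gap.

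**Step 2: position of each assessment.**

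| Assessment | Months since last counselling session, both arms | uTECH texting in the combined arm |
|---|---|---|
| Month 3 | 3 − 2 = 1 | ongoing, 12 − 3 = 9 months to run |
| Month 6 | 6 − 2 = 4 | ongoing, 6 months to run |
| Month 9 | 9 − 2 = 7 | ongoing, 3 months to run |
| Month 12 | 12 − 2 = 10 | at or about its end |

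At month 3, roughly 13 weeks × 2 = 26 of the 100 messages have been sent. An intercept difference there is post-counselling in both arms, but in the combined arm it arises early in uTECH delivery.

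**Step 3: what the contrasts identify.** Let d(t) be the added effect of uTECH at month t. The data inform d(3), d(6), d(9) and d(12). Take two scenarios with the same d at those four times:
- Lasting: d(t) stays at d(12) for t > 12.
- Dependent on texts: d(t) falls to 0 for t > 12.

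They differ only after month 12, where there are no assessments. They give identical distributions for everything the trial records, so no growth model, slope test or shift of the reference time point can tell them apart. The same data do inform whether d(t) is maintained or grows between months 3 and 12, that is, during texting.

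**The case against.** The strongest reply is that the protocol never defines durability as persistence after texts end. The version in This Study speaks of more sustained reductions. A natural reading is that counselling ends in month 2 and a year of texts helps to hold the gains. Comparing a continuing maintenance component with none is then the intended contrast, and the month 3 to 12 slope tests it. This stands. A reader might infer that the durability hypothesis cannot be tested at all, and the documents do not support that. Under the maintenance reading it can be tested. What cannot be tested is persistence after messaging stops.

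A reader might also infer that YMHP-only participants go without contact for 10 months. They do not. They complete surveys or interviews at 3, 6, 9 and 12 months, iOS users supply data downloads at 6 and 12 months, and Android users in both arms keep the eWellness app, which maps nearby services. The 10 months is time since the last counselling session.

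Nor could a durability claim be moved to YMHP itself. Both arms receive it, so no randomised contrast isolates its effect.

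Finally, these are secondary outcomes, Secondary Outcomes is worded tentatively, and the Discussion makes no claim of persistence. That limits the weight of the point but does not remove it. The abstract asserts more durable reductions as a hypothesis, and the two analysis sections describe follow-up in a way that is untrue for the combined arm. Messages carry an opt-out, so some participants may have text-free follow-up, but they would be self-selected and would not supply a randomised comparison.

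**Conclusion.** The point holds in a limited form. Persistence of any added uTECH effect after messaging stops cannot be assessed, because none of the four follow-ups in the combined arm falls meaningfully after texting ends, while all four in the YMHP-only arm come about 1, 4, 7 and 10 months after the last counselling session. The intercept and slope contrasts can show only whether reductions are greater and better maintained while texting continues. The durability wording in the abstract and Secondary Outcomes, and the post-intervention descriptions in Planned Analytic Approach and Missing Data, go further than that for the combined arm.

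This rests on texts being delivered as scheduled and on there being no assessment beyond those listed. It assumes texting starts at or soon after onboarding, since the article gives no start date. The primary outcomes of acceptability, appropriateness and feasibility, the sample size and the planned tests are unaffected.

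**What to change.** Change the wording in two groups of places.

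1. In the abstract (Methods), This Study and Secondary Outcomes, restate the hypothesis as: *greater reductions, maintained over 12 months while text messaging continues, than with YMHP alone*.
2. In Planned Analytic Approach and Missing Data, describe the month 3 to 12 contrasts as after YMHP counselling but during uTECH messaging. State that no claim of persistence after messages stop will be made from the slope or 12-month contrasts.

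Results states that data collection concluded in June 2024, so limiting the claim is the practical remedy. No change to the intervention schedule, models or tests is needed. The cost is a narrower claim on the secondary behavioural outcomes.

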**Results:**

This study was funded in August 2019. As of June 2024, all participants have been enrolled. Data analysis has commenced, and expected results will be published in the fall of 2025.

**Conclusions:**

This study aims to develop and test the acceptability, appropriateness, and feasibility of uTECH, a novel approach to reduce HIV risk and substance use among SGM young adults.

**Trial Registration:**

ClinicalTrials.gov NCT04710901; https://clinicaltrials.gov/study/NCT04710901

**International Registered Report Identifier (IRRID):**

DERR1-10.2196/58448

## Introduction

### Background

Sexual and gender minority (SGM) young adults are disproportionately affected by HIV in the United States, and substance use is a major driver of new infections. Among men who have sex with men (MSM) in the United States, the lifetime risk of receiving an HIV diagnosis is 1 in 6, compared to 1 in 524 among heterosexual men [1]. According to the 2022 Centers for Disease Control and Prevention (CDC) *HIV Diagnoses, Deaths, and Prevalence* report, approximately 70% of new HIV diagnoses were attributable to male-to-male sexual contact [2]. Young MSM are at particularly high risk for HIV and sexually transmitted infections (STIs). The CDC in the same report found that young people aged 13 to 34 years accounted for approximately half of all new HIV diagnoses in the United States in 2022. Transgender women in the United States have also been found to be at an increased risk for HIV [3]. A 2021 CDC report found that 4 in 10 transgender women surveyed in 7 major US cities are living with HIV [4]. While transgender women made up the large majority of new HIV diagnoses within transgender and gender nonbinary populations at 87%, HIV incidence among all these identities substantially rose between 2018 and 2022, with a staggering 136% rise in diagnoses among gender nonbinary persons, 33% in transgender men, and 24% in transgender women [2].

In the United States, evidence suggests that substance use is associated with condomless anal sex and increased numbers of sexual partners [5-9], both of which may increase one’s risk of HIV infection. MSM have been shown to be 3 to 4 times more likely to report substance use compared to the general population [10-12]. HIV infection among transgender women has also been associated with polysubstance use and sexual risk behaviors [13]. Compared to the populations of cisgender men and transgender women, little has been established in existing literature that examines the effects of sexual risk and substance use behaviors contributing to HIV and STIs in transgender men and gender nonbinary individuals. Our work uses the definition of *transgender* as individuals whose gender identity differs from their assigned sex at birth [14] and *gender nonbinary* as an umbrella term for individuals whose gender identity is neither man nor woman, encompassing a variety of experiences including but not limited to identification with multiple genders, no gender, or a gender that changes over time [15].

Lesbian, gay, and bisexual adults in the United States are approximately twice as likely to use web-based dating sites and apps compared to their heterosexual counterparts [16]. People who use web-based venues to meet sexual partners are more likely to report substance use, sexual risk behaviors, and STIs [17-19]. Geosocial networking apps, such as Grindr (Grindr, Inc) and Tinder (Match Group, Inc), use GPS to facilitate more efficient dating and networking with others based on proximity, which in turn may increase the likelihood of STI acquisition in specific geographical areas [20]. Research has also indicated that some MSM, transgender women, and gender nonbinary people use digital technologies to search for and intentionally use illicit drugs before or during sex to sustain, enhance, disinhibit, or facilitate the sexual experience, which may contribute to increased risk of HIV and other STIs through substance-induced disinhibition and increased length of sexual sessions [21,22].

Although web-based and social media data have been used by researchers in interdisciplinary fields for a range of health-related applications [23-25], to our knowledge, no interventions have been developed that use machine learning (ML) to inform HIV prevention and substance use harm reduction efforts for both MSM and other SGM populations. Previous research suggests the feasibility of applying social media and web-based data mining as a public health surveillance strategy [26-29]. ML, a branch of computer science that uses statistical and optimization tools to “learn” patterns and trends from large quantities of data, can be used to identify or predict new patterns or trends [30]. This approach has been used to detect and predict other health-related outcomes, such as preterm births [31], health care monitoring of patients with chronic illnesses [32], and suicide prevention [33]. On an individual level, insights gleaned from web-based and social media use patterns can inform cost-effective, scalable interventions that are highly personalized and delivered via technology (ie, tailored messaging and outreach from health workers).

The use of web-based and social media data mining and ML approaches within SGM populations for HIV prevention and substance use harm reduction has important implications for public health. Our team previously developed and tested a social media data mining program that correctly identified HIV risk and amphetamine and methamphetamine use using only social media data [34]. This system was refined and tested for this intervention trial.

There are few “best” rated evidence-based risk reduction interventions (EBRRIs) in the CDC Compendium of Prevention Research Synthesis for young adult, HIV-negative MSM. To our knowledge, there is currently 1 “best” rated EBRRI for young transgender women [35] and no “best” rated EBRRIs for other SGM populations, such as transgender men and gender nonbinary people. One of the few “best” rated EBRRIs for young gay and bisexual men is the Young Men’s Health Project (YMHP), which is a manualized 4-session intervention that uses motivational interviewing (MI) and problem-solving skills to provide personalized feedback for reducing risk behaviors and promoting HIV prevention skills such as using HIV pre-exposure prophylaxis (PrEP) [36]. It is also the only intervention to show significant effects in reducing both condomless anal sex and substance use. YMHP has also been effectively used in remote delivery [37]. The YMHP intervention component, MI, is a proven approach in HIV or STI prevention for many populations [38,39]. However, few research studies have tested the effectiveness of MI for risk reduction with other SGM people, including transgender women, transgender men, and gender nonbinary young people [40,41].

### This Study

We hypothesize that the uTECH+YMHP intervention will be considered acceptable, appropriate, and feasible by most participants. Furthermore, we hypothesize that participants receiving the combined uTECH+YMHP intervention will show greater and more sustained reductions in substance use and sexual risk behaviors compared to those receiving the YMHP intervention alone. Specifically, we anticipate that the integration of ML-informed SMS text messages will enhance the efficacy of YMHP counseling methods by providing personalized, timely, and contextually relevant support, ultimately leading to improved health outcomes in this sample of SGM young adults.

